#### Expectations

As there is no current gold standard for characterizing patient expectations of TKA outcomes, we will be adopting a mixed methods approach and using both standardized self-report, closed-response surveys and open-ended questions to quantify patient expectations and changes in these expectations over time. To evaluate the change in expectations, all participants will be asked to complete the following questionnaires at study entry and following the intervention.

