#### Direct Questioning of Objectives Questionnaire

Methods comparable to those applied by Karunaratne et al [70], using open-ended questions related to participant expectations, will be applied. Participants will be asked to list at least 1 and up to 5 of their most important expectations of TKA surgical outcomes, and then an assessment will be given for two domains for each expectation on 11-point numerical rating scales: (1) the importance of each expectation and (2) the current ability to achieve the task / item. The reported values for importance and ability will be interpreted as “low” if ≤5, and “high” if ≥8. A Direct Questioning of Objectives Questionnaire Index (DQO Index) will be derived from the product of the score for each domain.

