#### Expectation Fulfillment

The level of expectation fulfillment or satisfaction to undertake goals identified will be determined at 6 months after TKA for participants who proceeded with surgery.

For the HSS-TKR items, participants will be asked to indicate the extent of fulfillment of the expectations, identified prior to surgery, using a 5-point Likert scale, ranging from 5 (completely) to 1 (not at all).

The DQO Index will be repeated post TKA, and differences with values obtained prior to TKA will be indicative of the ability to achieve the task.

For activity expectations identified in the pre-TKA assessment, participants will be asked to rate how satisfied they were that each activity could be undertaken using a 7-point Likert scale ranging from 1 (completely dissatisfied) to 7 (completely satisfied).

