### Secondary Outcomes

The following secondary outcomes will also be evaluated:

The number of participants who decide not to proceed with their TKA.The level of patient expectation fulfillment derived from the HSS-TKR questionnaire, the DQO Index, and activity expectations, conducted 6 months after the TKAThe level of patient satisfaction with surgical outcomes assessed at 6 months after the TKA.A change in patient health literacy (within individual patients’ scores), derived from the HLS-EU-Q12, conducted at study entry and at 6 months after the TKA

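### The 6-month DQO fulfilment measure is a change in importance × ability, so it does not isolate the ability it is said to indicate

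*Protocol article*

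**What the plan says.** Under Direct Questioning of Objectives Questionnaire, each patient lists up to five goals and gives two ratings for each, "1) the importance of each expectation and (2) the current ability to achieve the task / item", on "11-point numerical rating scales". Ratings of either kind "will be interpreted as “low” if ≤5, and “high” if ≥8", so a higher number means more important or more able. The section then states: "A Direct Questioning of Objectives Questionnaire Index (DQO Index) will be derived from the product of the score for each domain".

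Under Expectation Fulfillment, that same Index is repeated after TKA, and the "differences with values obtained prior to TKA will be indicative of the ability to achieve the task". Secondary Outcomes makes it part of a listed outcome at 6 months: "The level of patient expectation fulfillment derived from the HSS-TKR questionnaire, the DQO Index, and activity expectations".

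There are two pre-surgery administrations, since "all participants will be asked to complete the following questionnaires at study entry and following the intervention". The article does not say which of them is the reference for the 6-month difference. It also does not say that importance is held at a pre-surgery value, or that the ability rating is analysed on its own.

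**The concern.** The stated interpretation does not follow from the stated formula. A difference between two products responds to both factors, so it can indicate ability only if importance is constant or held fixed.

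This matters more here than for a neutral weight. The DQO is given before and after the intervention precisely to detect change in expectations, and Data Analysis (Stage 2) compares within-patient changes in the open-ended measures between arms. The Background cites earlier education that lowered expectations and raised fulfilment. One of the two multiplied quantities is therefore something the programme could plausibly alter. If it does, the arms can differ on the Index change when patients recovered equally. The aim that depends on this is whether the programme is associated with better expectation fulfilment.

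**Working it through.** **Inputs.** The formula (importance × ability) and the repetition of the Index come from the article. The end points of the 11-point scale are not printed; 0 to 10 is assumed. The article gives no mean, SD or expected shift for any DQO rating, so there is no plan figure to reproduce, and every rating below is illustrative.

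**Notation.** I is importance, A is ability; subscript 0 is the pre-TKA reference and 6 is 6 months. The measure is I₆A₆ − I₀A₀.

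**Step 1: one patient, importance alone moves.**
- Ability fixed at 4, importance 6 to 10: 10×4 − 6×4 = 40 − 24 = +16, with no ability gain.
- Ability fixed at 5, importance 9 to 6: 6×5 − 9×5 = 30 − 45 = −15, with no ability loss.

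**Step 2: same ability gain, different importance at 6 months.** Ability goes from 2 to 8 and starting importance is 10.
- Importance stays at 10: 80 − 20 = +60.
- Importance falls to 4: 32 − 20 = +12.

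**Step 3: between arms, identical ability paths.** A control patient keeps importance I throughout. A programme patient starts at I and drops by d after the intervention. Ability goes from A₀ to A₆ in both.
- Control: I(A₆ − A₀).
- Drop persists, baseline reference: (I − d)A₆ − I·A₀ = control − d·A₆.
- Drop persists, post-intervention reference: (I − d)(A₆ − A₀) = control − d(A₆ − A₀).
- Drop recovers by 6 months, baseline reference: equal to control.
- Drop recovers by 6 months, post-intervention reference: I·A₆ − (I − d)A₀ = control + d·A₀.

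With I = 9, d = 3, A₀ = 3 and A₆ = 8:

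| Patient | Baseline reference | Post-intervention reference | Ability change |
|---|---|---|---|
| Control, importance 9 throughout | +45 | +45 | +5 |
| Programme, importance 9, then 6, stays 6 | +21 | +30 | +5 |
| Programme, importance 9, then 6, back to 9 | +45 | +54 | +5 |

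Over the whole 0–10 grid, all 3,025 combinations with improved ability and persistently lower importance give the programme patient a smaller change than the control, under either reference. If ability worsens, a persistent drop with the post-intervention reference gives a smaller loss, so the direction reverses.

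**Step 4: what this could do to a comparison.** Assume 64 per arm, three goals per patient, importance about 9 (SD 1.2), and ability 3 before and 7 after in both arms. Suppose a 1-point importance drop that persists. The share of trials with P<.05 on the Index change ran from 21% to 60% (post-intervention reference) and from 57% to 96% (baseline reference) as the assumed ability SD went from 3 down to 1.5. For a 0.25-point drop it was 6–7% and 8–13%. A temporary 1-point drop, with ability SD 2, favoured the programme by about 3 points with the post-intervention reference (P<.05 in 28%) and showed no bias with the baseline reference (4%). The change in ability alone stayed near 5%. These rates also move with how ratings are truncated at the ends of the scale, so they show only that the effect can be material.

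**The case against.** Four arguments deserve weight.

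1. **Re-rating is not stated outright.** The article says the Index is repeated, not that importance is scored afresh, and Table 1 lists the Index before surgery but only the questionnaire at 6 months. If importance were carried forward, Step 1 would fall away. Repeating an index that has two rated domains most naturally means rating both, however. Even carried forward, the gain is still weighted: an ability gain of 5 scores 6×5 = 30 or 9×5 = 45.

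2. **A condensed article may leave scoring to the full protocol, and the method follows a cited study.** That would excuse a missing detail. Here the article states both the formula and the interpretation, and the two do not agree.

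3. **A bias against the programme is not established.** A reader might infer that a successful programme must score as worse fulfilment despite equal recovery. The documents do not support that. Nothing says the programme lowers DQO importance ratings. The goals are the patient's own most important ones, so a persuaded patient may list a different goal and rate it just as highly. The direction also depends on whether a drop lasts and on the reference visit. This objection stands and limits the point.

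4. **Weighting by importance is a legitimate choice.** It is, as a measure of importance-weighted achievement, but such a measure should not be read as ability. This argues for keeping the product as a supporting result. It does not rescue the stated interpretation.

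**Conclusion.** The point holds in a limited form. On the natural reading that both domains are rated again at 6 months, the Index difference is not a measure of ability; that is algebra and needs no assumed data. A bias between arms is conditional on the programme changing importance ratings. It then runs against the programme if the fall lasts and ability improves. If importance recovers, the bias is nil with the baseline reference and in the programme's favour with the post-intervention reference. Its size cannot be fixed from the article, and the rejection rates above rest wholly on assumed inputs. Nor should they be called type I error for the Index itself: when importance differs, the Index really does differ between arms. The error lies in reading that difference as ability.

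The reach is modest: one of three fulfilment measures within one of four secondary outcomes. HSS-TKR fulfilment and activity satisfaction are rated directly, and the primary outcome and sample size are untouched. It is still worth correcting before outcome data are seen.

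**What to change.** In Expectation Fulfillment and Secondary Outcomes, define DQO fulfilment as the 6-month ability rating minus the pre-TKA ability rating for the same pre-listed goals, averaged over each patient's goals, and name the pre-TKA visit that serves as reference. Report importance at each visit separately. If the product is kept, present it only as a supporting result with importance held at that one pre-TKA visit.

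On this measure every patient in the Step 3 table scores +5, and a patient whose ability is unchanged scores 0 whatever happens to importance.

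The cost is wording and derivation only, since both ratings are already collected. The small downside is that all of a patient's goals then count equally, which the supporting importance-weighted result would partly offset. The ability change also has less headroom for patients who list goals they can already partly do, so ability at the reference visit should be reported by arm.

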#### Satisfaction

At 6 months after the TKA, all participants who underwent surgery will be asked to respond to the following:

*Overall, how would you describe the results of your operation?*

Participants will provide a response on a 5-point Likert scale, ranging from 1 (poor) to 5 (excellent).

#### Feedback Survey

A study participation evaluation survey will be included at the end of the study to enable participants to provide the research team with feedback regarding the intervention and assessments they were asked to undertake and the overall conduct of the study. It will also give study participants the opportunity to provide ideas for future areas of research they consider important to be addressed in recovery from TKA surgery. For those who did not proceed with undergoing a TKA, information will be collected regarding alternate treatment procedures they have undertaken.

### Primary Outcome

The primary outcome of the trial will be a change in patient postsurgical expectation score (within individual patients’ scores), derived from the HSS-TKR questionnaire, conducted prior to and following intervention exposure.

### Secondary Outcomes

The following secondary outcomes will also be evaluated:

The number of participants who decide not to proceed with their TKA.The level of patient expectation fulfillment derived from the HSS-TKR questionnaire, the DQO Index, and activity expectations, conducted 6 months after the TKAThe level of patient satisfaction with surgical outcomes assessed at 6 months after the TKA.A change in patient health literacy (within individual patients’ scores), derived from the HLS-EU-Q12, conducted at study entry and at 6 months after the TKA

### Data Analysis

#### Stage 1

A Method Triangulation approach will be taken in the alpha testing of the developed educational program, encompassing the participant responses to the PEMAT-A/V survey and content analysis of structured interviews [74]. This will inform editing or adjustments to the prototype videos to enable the final version to be generated and evaluated in stage 2.

##### PEMAT-AV Tool

Two subscores will be derived from the provided survey ratings, including the understandability and actionability scores. These scores will be provided as the total points (agreement with the statements provided) for each domain, expressed as a percentage of the total possible points. Higher scores will be indicative of good understandability and clarity of the actionability of the information provided in the videos. The scores and responses provided for each statement in the survey will be used to formulate the topics addressed in the subsequent interview between the participant and the researcher.

##### Content Analysis of Qualitative Data

The interviews will be conducted by either research team member (KR or LS) during a 30-minute, one-to-one session with the research participant. Each interviewer will review the transcript and validate the content, such that it reflects the PEMAT-AV scores for each video. The content concepts will be identified to reflect the acceptability of the prototype videos or potential changes or edits that need to be considered by the research team. To assist with ensuring the dependability of the data, the interviewers will then review the content analysis undertaken by the other interviewer and again undertake their own validation and identification of content concepts for each transcript. Both interviewers will then meet and compare each one’s content analysis and discuss until a consensus is reached. Coding will be undertaken such that classifiers will be applied to the common concepts identified across all transcripts. The interviewers will then determine if content saturation has been achieved or if additional participants will need to be recruited for the alpha testing.

### Stage 2

Descriptive and inferential statistical analyses will be undertaken to describe the characteristics of the participant cohort and to assess the research hypotheses, respectively. Clinical and demographic characteristics will be described using proportions, measures of central tendency (eg, mean and median), and dispersion (eg, SD, IQR). Inferential statistics will be used to test for differences in, or associations between, outcome measures within and between groups of interest. Methods appropriate to both dependent and independent samples (eg, *t* test, ANOVA, and correlation) will be used, including nonparametric methods for data in violation of normality and variance assumptions (eg, Mann-Whitney *U* and Kruskal-Wallis). The threshold for statistical significance will be set at a *P* value of .05.

To determine the impact of the health education program to change expectations, the primary outcome measure (HSS-TKR) will be measured and compared between the 2 treatment arms. The within-patient changes of the open-ended measures of patient expectations between T_0_ and T2 will also be compared between the 2 treatment arms to further inform the efficacy of the education platform intervention. We will use data from all participants post surgery to determine the association between expectation fulfillment and overall satisfaction. Activity expectation fulfillment satisfaction and overall procedure satisfaction generate ordinal datasets with associations between the 2 measures undertaken using Spearman rank correlation coefficients.

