The impact of educational materials generated in stage 1 will be evaluated in a longitudinal, parallel group, 2-armed, block randomization trial with an allocation ratio of 1:1 [59]. Patients undergoing TKA will be enrolled when they have been scheduled for the surgical procedure and will be involved in study assessments for a total of 32 weeks (8 months) from study entry. Referrals of potential study participants will be provided by the participating orthopedic surgeons when their patient has consented to undergo a TKA. The maximum wait time between patient consent and surgery taking place is 6 weeks. Consequently, all presurgery assessments and the study intervention will take place within this 6-week window. Following study consent, baseline assessments will be undertaken at study entry, which is likely to be 5 weeks prior to TKA. The intervention (viewing the educational videos+standard care) or control (standard care alone) will be delivered 4 weeks prior to the scheduled TKA. Standard care will encompass any educational materials provided to the patient by their surgeon and health care provider. For the intervention group, participants will be provided online access to the educational videos. They will have the capacity to view the videos several times if they desire and will record the number of times each one is viewed. Postintervention assessments will be conducted 3 weeks prior to TKA, and postsurgical outcome measures will be undertaken at 6 months following the TKA.

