### Sample Size

#### Sample Size Estimation and Justification

##### Stage 1

We will initially involve 5 individuals who have undergone a TKA within the last 5 years to take part in video alpha testing encompassing the understandability and actionability of the prototype of the educational videos. Content analysis will be via an inductive approach [60]. If we find that the issues identified in the prototype videos differ substantially between each participant and saturation of the feedback content is not occurring, we will enroll 5 further individuals to undertake the alpha testing, such that feedback from up to 10 individuals will be included in stage 1. The purposive sampling approach being adopted will enable a diverse group of viewpoints to be derived. Taken together with the collaborative approach between the stakeholder groups involved in the design component of this study, we are confident that the number of participants involved in the alpha testing is sufficient to support the development of education materials to be further evaluated in stage 2 of this study.

##### Stage 2

A sample of 150 individuals who have been identified as requiring a TKA by their treating orthopedic specialist (2 subgroups of n=75) will be recruited. This will allow for expected dropouts (approximately 22/150, 15%) and ensure a minimum sample size of 64 for each group, which will enable the study to be adequately powered (see calculations below). A screening log will be kept and will collate reasons why any participants were screened but did not take part in the study.

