### Power Calculation: Sample Size Estimate

The number of participants was selected based on previously published findings using the Hospital for Special Surgery Total Knee Replacement Expectations Survey (HSS-TKR) as our primary outcome measure to demonstrate a clinically meaningful change in the overall patient expectation score [35]. Mancuso et al [35] describe a clinically meaningful change in expectations to be associated with a 6-point change in transformed HSS-TKR total scores. To determine a significant difference between 2 groups of patients, such that α=.05, power 80%, and SD 12, will require 64 patients per group. In this study, we will enroll 75 patients per treatment arm to allow for any potential loss of participation at the follow-up time points.

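### The stated fallback to rank tests when normality or variance assumptions fail reaches the HSS-TKR primary outcome, does not repair unequal variances, and leaves the 6-point mean difference that the trial is sized on

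*Protocol article*

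**What the plan says.** Under Data Analysis, Stage 2, the article lists the t test, ANOVA and correlation as examples of its methods and adds "including nonparametric methods for data in violation of normality and variance assumptions", giving Mann-Whitney U and Kruskal-Wallis as examples. The Methods part of the Abstract repeats the rule without the examples. In both places the sentence covers outcome measures in general.

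The paragraph that follows in Data Analysis says that HSS-TKR will be compared between the two arms but names no test for it. The one outcome-specific method named there is Spearman correlation, for activity satisfaction against overall satisfaction.

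The Power Calculation section takes from a published study "a clinically meaningful change in expectations to be associated with a 6-point change in transformed HSS-TKR total scores". It then states that "α=.05, power 80%, and SD 12, will require 64 patients per group". That is a comparison of two means.

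**The concern.** The rule treats non-normality and unequal variance as one problem with one remedy. For unequal variance the remedy does not work. A rank-sum test can be read as a test of shift only if the two arms share shape and spread. Otherwise it tests whether a patient in one arm is equally likely to score above or below a patient in the other, which is not whether the means are equal. It also gives no estimate of the 6-point mean difference.

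Since nothing exempts HSS-TKR, the quantity tested in the primary analysis would depend on how the outcome data look. The trigger is plausible in this trial. The programme aims at unrealistic expectations, so it may move some patients a long way and others little, which would make the intervention arm skewed and more variable. That is a reasoned assumption; the article reports no distribution of change scores.

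**Working it through.** **Inputs from the article.** Difference 6 points, SD 12, alpha 0.05, power 80%, 64 per group (Power Calculation); 1:1 allocation (Methods, Stage 2). SD 12 is taken as the within-arm SD of the quantity compared. The test is taken as two-sided, because only that reproduces 64; a one-sided test would give 50.

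**Inputs assumed.** The shapes, the SD ratios and the trigger. The article gives no formal trigger; Shapiro or Levene at 0.05 is assumed here.

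**Step 1: the plan's own figure.** n = 2 × (1.96 + 0.8416)² × 12² / 6² = 62.8, so 63 by the normal approximation. The exact two-sample t test gives 63.8, so 64, with 80.1% power. The figure reproduces, and it is a mean-difference calculation.

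**Step 2: rejection rate when the true means are equal** (20,000 simulated trials, 64 per arm unless stated).

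| Setting | Pooled t | Welch t | Mann-Whitney |
|---|---|---|---|
| Identical normal, SD 12 | 5.0% | 5.0% | 5.0% |
| Identical exponential, SD 12 | 5.0% | 5.0% | 5.2% |
| Normal, SD 8 v 16 | 5.2% | 5.1% | 6.0% |
| Normal, SD 6 v 18 | 5.2% | 5.1% | 7.1% |
| Normal, SD 8 v 16, 75 v 53 patients | 7.6% | 4.9% | 7.3% |
| Exponential, SD 10 v 14 | 5.0% | 4.9% | 23.0% |
| Exponential, SD 8 v 16 | 5.1% | 5.1% | 47.1% |

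Unequal spread alone does little harm with equal arms. Skew combined with unequal spread does much more. In those last two rows, however, the distributions differ, so the rank test is detecting a real difference that is not a difference in means.

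**Step 3: power when part of the arm responds.** Let 30% of intervention patients fall by 20 points and the rest not change, with SD 12 throughout.

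- Mean effect: 0.30 × 20 = 6 points.
- Intervention-arm variance: 144 + 0.30 × 0.70 × 20² = 144 + 84 = 228.
- Standard error: √((144 + 228)/64) = 2.41.
- Power of the mean comparison: Φ(6/2.41 − 1.96) = Φ(0.53) ≈ 70%.

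Simulation of the switching rule in this setting gives about 65%, a loss of about 5 points. With SD 8 throughout, the figures are 91% for the t test and 79% with switching, but SD 8 is not a figure from the article.

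**Step 4: settings that go the other way.** For a pure 6-point shift with t(3) tails, the t test has 83% power and Mann-Whitney 97%. For a pure shift of an exponential shape, 80% and 98%. For a normal shift, 80.3% and 78.4%.

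**Step 5: a remedy that keeps the mean.** Welch's test holds 4.8% to 5.4% error in all the normal settings tried, including an SD ratio of 1:3 and 75 v 53 patients. In the skewed settings at 64 per arm it holds 4.8% to 5.8%. Its power for 6 points is 80.3% with SD 12 in both arms, and 79.8% with SDs of 8 and about 15 (the same average variance).

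**The case against.** The strongest reply is that the sentence is generic. It covers many outcomes, several of them ordinal (the 5-point satisfaction item, the 7-point activity ratings), for which rank methods are right. The article is condensed, and an analysis plan that is not shown may name the primary test. This stands in part: leaving the test to that plan would be no fault. But the article does state a remedy, names variance violation as a ground for it, and exempts nothing.

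Four stronger readings are tempting and are not supported:

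- **A general inflation of false positives.** If the programme changes nothing, the two distributions are identical and the rank test keeps about 5%; so does the switching rule (4.8% to 5.1% in simulation). A scenario in which 25% of patients fall by about 18 points and 75% rise by about 6, so that the mean cancels, gives 12% to 14% rejections, but only with an SD of 8. With the article's SD of 12 it gives 5% to 6%. In that scenario the programme also changes every patient, so a rejection is not false in the ordinary sense.
- **A general loss of power.** Step 4 shows large gains with heavy tails or a pure shift of a skewed shape.
- **That rank tests would drop baseline and provider adjustment.** The article specifies no adjusted analysis. Health care provider is a stratification variable only, and the t test that it names does not adjust either.
- **That the sample size is wrong.** It reproduces.

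**Conclusion.** The point holds for the HSS-TKR primary outcome. The stated rule lets the data move the primary test away from the powered mean difference, to a test that does not cure one of the two faults it is prescribed for. This follows from the wording and needs no distributional assumption.

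The numerical harm does need one. It runs from nothing (identical distributions), through about 1 percentage point of excess rejection (normal data, SD 8 v 16, equal arms) and about 5 points of lost power (30% responders, SD 12), to far larger distortions of a test of equal means if skew and unequal spread coincide. In some shapes the rank test does better. The change is worth making before outcome data are seen, because it settles what the trial estimates. It is not evidence that the trial would mislead.

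**What to change.** In Data Analysis, Stage 2, name one primary analysis for HSS-TKR, to be used whatever the distribution: ANCOVA of the post-intervention score on the baseline score and health care provider, with heteroscedasticity-robust standard errors. Report the adjusted mean difference with its 95% confidence interval. Move the rank test for HSS-TKR to a labelled sensitivity analysis. Confine rank or ordinal methods to the ordinal outcomes, such as overall satisfaction and the activity ratings. Remove unequal variance as a ground for switching to rank tests, and align the Abstract.

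The cost is wording. Baseline HSS-TKR is already collected and provider is already a stratification factor. The 64 per group is unchanged. The downsides are a negligible loss of efficiency from robust errors and, if the changes prove heavy-tailed, possibly less power than a rank test would have had.

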### Aims and Objectives

In the current project, we will collaboratively develop a novel educational program for patients undergoing TKA with orthopedic care teams, consumer advocates, and key health care provider stakeholders, which will focus on providing information that will inform and encourage patients to set realistic expectations of TKA surgical outcomes. The ability of the program to influence the type of expectations patients set prior to surgery will be assessed by comparing patients’ expectations before and after the program and by comparing expectations of those who participate in the program to those who receive “standard clinical care” alone. In addition, the project will determine if education program participation is associated with a higher level of expectation fulfillment, satisfaction with surgical outcomes, and improvement in health literacy. We will apply a number of different methods to define patients’ expectations, using both closed- and open-ended questionnaires to evaluate the scope of responses achieved by each approach.

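### The primary HSS-TKR comparison names only unadjusted methods although every participant has a baseline score; one baseline-adjusted between-arm ANCOVA would gain precision at no cost

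*Protocol article*

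**What the plan says.** The Primary Outcome section sets the endpoint: "The primary outcome of the trial will be a change in patient postsurgical expectation score", taken within individual patients from before to after the intervention. Table 1 and the Expectations section show that every participant completes HSS-TKR at both of those times.

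Under Data Analysis, Stage 2, the effect of the programme is to be judged as follows: "the primary outcome measure (HSS-TKR) will be measured and compared between the 2 treatment arms". That sentence names no test, model or covariate. The preceding paragraph lists the t test, ANOVA and correlation as examples, with Mann-Whitney U and Kruskal-Wallis as nonparametric alternatives. The list covers all outcomes, and both within-group and between-group comparisons.

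The Power Calculation section takes its target from a cited study, which found "a clinically meaningful change in expectations to be associated with a 6-point change in transformed HSS-TKR total scores". It then states that "α=.05, power 80%, and SD 12, will require 64 patients per group". It does not say whether 12 describes a score at one time or a change between two times.

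Aims and Objectives plans two kinds of evidence, comparing patients' "expectations before and after the program and by comparing expectations of those who participate in the program to those who receive" standard care alone. The Stratification section makes health care provider a stratification variable, because standard education may differ between providers and may influence expectations.

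**The concern.** Baseline HSS-TKR is likely to be the strongest available predictor of the post-intervention score, and it is already collected. None of the named methods adjusts for it. Subtracting the baseline to form a change does use it, but with a fixed coefficient of 1. Unless the correlation is perfect (with equal variances at the two times), that coefficient is too large. The change score then carries extra noise and over-corrects any chance difference between the arms at baseline. ANCOVA estimates the coefficient from the data.

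The unlabelled SD adds to this. Whether a change-score test delivers the planned 80% depends on what the 12 describes, and the text does not settle it.

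The before-after comparison is a separate weakness. The intervention arm also receives standard education, and everyone answers the questionnaire twice. A shift within that arm cannot be credited to the videos alone.

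**Working it through.** **Inputs from the article.** Difference 6 points, SD 12, significance level .05, power 80%, 64 per group (Power Calculation); allocation 1:1 (Stage 2 design). Sidedness is not stated. I take it as two-sided, because that reproduces 64 while one-sided gives 50.

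**Assumptions.** r, the correlation between baseline and post-intervention HSS-TKR, is not given; I show 0.3 to 0.8. The SD is taken as equal at the two times.

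**Step 1: reproduce the plan's figure.** Standardised difference = 6/12 = 0.5. The normal approximation gives n = 2 × (1.960 + 0.842)² × 12²/6² = 62.8, so 63. The t-based calculation gives 63.8, so 64 per group. Power at 64 per group is 80.1%. The stated figure reproduces as an unadjusted two-sample comparison.

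**Step 2: SD to be used under each analysis.**
- If 12 is the score SD: change SD = 12√(2(1 − r)); ANCOVA residual SD = 12√(1 − r²).
- If 12 is the change SD: change SD = 12; ANCOVA residual SD = 12√((1 + r)/2).

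Under either reading the ratio of ANCOVA variance to change-score variance is (1 − r²)/(2(1 − r)) = (1 + r)/2. It is below 1 whenever r is below 1. At r = 0.3 it is 0.65, at 0.5 it is 0.75 and at 0.8 it is 0.90.

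**Step 3: power at 64 per arm for 6 points**, from the two-sample t test with the SD of step 2. The few degrees of freedom spent on covariates are ignored.

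| r | Score SD = 12: change test | Score SD = 12: ANCOVA | Change SD = 12: change test | Change SD = 12: ANCOVA |
|---|---|---|---|---|
| 0.3 | 66% (SD 14.20) | 84% (SD 11.45) | 80% | 94% (SD 9.67) |
| 0.4 | 73% (SD 13.15) | 86% (SD 11.00) | 80% | 92% (SD 10.04) |
| 0.5 | 80% (SD 12.00) | 90% (SD 10.39) | 80% | 90% (SD 10.39) |
| 0.7 | 95% (SD 9.30) | 98% (SD 8.57) | 80% | 86% (SD 11.06) |
| 0.8 | 99% (SD 7.59) | >99% (SD 7.20) | 80% | 84% (SD 11.38) |

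ANCOVA is ahead in every row under both readings and never falls below 80%. The change-score test falls below 80% only if 12 is the score SD and r is below 0.5.

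**Step 4: the before-after comparison.** No arithmetic is needed. Aims and Objectives counts it among the ways the programme will be assessed, and Data Analysis, Stage 2 provides for within-group tests. The Stage 2 design gives standard care to both arms. Anything that moves both arms alike, whether standard education or answering the survey a second time, appears in full in a within-arm test and cancels only in the between-arm contrast.

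**The case against.** The strongest reply is that the article has not chosen an unadjusted test. Its methods are examples for all outcomes, the sentence on the primary comparison names none, and a condensed article may leave the model to an analysis plan that is not shown. That stands: a reader might infer that a t test is fixed for the primary outcome, and the text does not support this. What remains is that every method it does name is unadjusted, so the better choice is worth writing down.

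Second, baseline is not ignored, and a randomised comparison of changes is unbiased. That also stands, and it is why the gain is one of precision.

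Third, a reader might infer from the 66% and 73% that the trial is underpowered. The documents do not show that. Those figures need 12 to be the score SD and r to be below 0.5, and neither is stated. The 12 follows directly on a 6-point change, so the change SD is at least as natural a reading, and on it the change-score test already has 80%. The two assessments are planned about two weeks apart (5 and 3 weeks before surgery), and nothing in the article points to a low correlation.

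Fourth, a reader might take the before-after test to be the primary comparison, or hold that standard education is known to shift expectations. Data Analysis, Stage 2 rests the effect on the primary outcome on the comparison between arms, and the Stratification section says only that differing standard care may influence expectations. The documents give no size for any drift common to both arms, so no false-positive rate can be attached to the within-arm test.

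**Conclusion.** The point holds as an efficiency improvement that costs nothing. The sample size is correct on its own inputs. Relative to a change-score comparison, ANCOVA cuts the variance by 35% at r = 0.3, 25% at r = 0.5 and 10% at r = 0.8, whichever SD the 12 is. In power, that means 84% to 94% instead of 80% if 12 is the change SD. If 12 is the score SD, the gain runs from 18 percentage points at r = 0.3 to about 2 at r = 0.7 (95.2% to 97.6%) and less above that. These sizes rest on the assumed range of r, equal variances at the two times and 64 analysed per arm.

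The lack of a label on the SD is a reporting gap that should be closed with it. The within-arm comparisons are legitimate description, but they should not count as evidence that the programme works.

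**What to change.** - Name one primary analysis: ANCOVA of the post-intervention transformed HSS-TKR score on arm, with baseline HSS-TKR and health care provider (the stratification variable) as covariates, reporting the adjusted mean difference with its 95% CI. With baseline in the model, the arm effect is the same whether the dependent variable is the post score or the change, so the endpoint as defined is kept.
- Analyse HLS-EU-Q12 in the same way, with the 6-month score as the dependent variable and its own baseline as covariate.
- State in the Power Calculation whether 12 is the SD of the score or of the change, and that the test is two-sided.
- State that effectiveness rests on the between-arm estimate and that within-arm before-after changes are descriptive.

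The cost is analysis wording only: the baseline scores and the provider are already recorded, and no patients, visits or questionnaires are added. The wording should be settled before outcome data are analysed.
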